## Abstract

**Background:**

Cervicogenic headache is a prevalent and costly pain condition commonly treated by chiropractors. There is evidence to support the effectiveness for spinal manipulation, but the dose of treatment required to achieve maximal relief remains unknown. The purpose of this paper is to describe the methodology for a randomized controlled trial evaluating the dose–response of spinal manipulation for chronic cervicogenic headache in an adult population.

**Methods/Design:**

This is a mixed-methods, two-site, prospective, parallel groups, observer-blind, randomized controlled trial conducted at university-affiliated research clinics in the Portland, OR and Minneapolis, MN areas. The primary outcome is patient reported headache frequency. Other outcomes include self-reported headache intensity, disability, quality of life, improvement, neck pain intensity and frequency, satisfaction, medication use, outside care, cervical motion, pain pressure thresholds, health care utilization, health care costs, and lost productivity. Qualitative interviews are also conducted to evaluate patients’ expectations of treatment.

**Discussion:**

With growing concerns regarding the costs and side effects of commonly used conventional treatments, greater numbers of headache sufferers are seeking other approaches to care. This is the first full-scale randomized controlled trial assessing the dose–response of spinal manipulation therapy on outcomes for cervicogenic headache. The results of this study will provide important evidence for the management of cervicogenic headache in adults.

**Trial registration:**

ClinicalTrials.gov (Identifier: NCT01530321)

## Background

Headaches are a common, disabling condition with a substantial public health and financial impact on society [1]. Approximately half to three quarters of the global population experiences a headache during their life [2], and the financial costs on society are huge. It is estimated that 157 million days of work are lost each year due to headaches, costing approximately $50 billion in work absenteeism and medical benefits [3]. Neck pain is common among headache sufferers [4], and secondary headache pain referred from a neck disorder is defined as cervicogenic headache (CGH) [5]. The point prevalence for CGH ranges from 0.4 to 4.6% [6–8] and up to 18% of the chronic headache population due to variation in its definition [9].

Because of the growing concerns about harmful side effects from over utilized pain medication [10], there is a great need to investigate effective, safe, and cost-effective complementary and integrative health therapies for headache conditions. About 34% of US adults use such therapies annually [11], many for headache and neck pain [12, 13]. Spinal manipulative therapy (SMT), a commonly used treatment for headache [4], is among the most common [14].

A growing body of literature supports the use of SMT for headache and no other intervention has been shown to be superior for the care of CGH [15–18]. Efficacy of SMT for the relief of chronic CGH has been summarized in systematic reviews [15, 19]; one review however found insufficient evidence to reach a conclusion [20]. Most randomized controlled trials found evidence of efficacy for SMT for CGH frequency, intensity and duration [4, 21–23], specifically compared to deep massage [24] and no treatment [25]. Despite this, there remains little consensus on what constitutes an appropriate dose of manipulation needed to achieve maximal benefit [26–30]. Preliminary studies suggest a dose–response relationship for SMT in the management of CGH [27, 29]. One pilot RCT (*n* = 24) examined differences between three doses: 3, 9, or 12 SMT visits and found preliminary benefits with larger doses [27]. A second (*n* = 80) compared 8 and 16 SMT visits and found clinically important differences between SMT and the control and small differences between the two doses for a number of headache outcomes [29]. This is the first full-scale randomized controlled trial to investigate this relationship.

### Study aims

The primary aim is to determine the effect of SMT visits on self-reported clinical outcomes and objective physical measures in 256 adults with chronic CGH (≥3 months), measured at 12 and 24 weeks. The primary outcome is patient-rated CGH frequency measured in days in the 4 weeks prior to these time points. Our hypothesis is that a greater number of SMT treatments leads to a greater reduction in CGH frequency. The secondary aim is to determine the cost-effectiveness and cost-utility of the number of SMT treatments for the care of chronic CGH. The tertiary aim is to assess the effects of expectations on outcomes using mixed-methods in order to gain a better understanding of how patients view their headaches and treatment.

## Methods/Design

### Study overview

This study is a two-site, prospective, parallel groups, observer-blinded, randomized controlled trial. The trial began in August 2012. Participants are recruited at Northwestern Health Sciences University in Bloomington, MN and the University of Western States in Portland, OR. Study treatments are provided within university-affiliated outpatient clinics. The study design is based on a previous pilot randomized controlled trial [29].

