### Data collection

Patient self-reported outcomes are collected at baseline and 6, 12, 24, 39, and 52 weeks post randomization using headache diaries and questionnaires. Objective spinal biomechanical outcomes and pain pressure thresholds are collected at BL1 and at 6 weeks (end of treatment). Qualitative interviews are also conducted at the end of treatment. Study data is managed using Research Electronic Data Capture (REDCap) tools hosted at the University of Western States [37].

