#### Tertiary AIM: effects of expectations

##### Qualitative interviews

One-on-one (face to face), semi-structured qualitative interviews are conducted by trained research staff at week 6. An interview schedule is used to direct the interviews and keep interviewers on track with the study’s objective. Participants are asked about their treatment views, expectations and lived experience with headaches. Questions start broadly and are followed-up with probing questions to elicit additional information.

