### Blinding

Research staff who perform clinical and objective examinations and data entry are blinded to treatment assignment. Providers and participants are initially blinded to dose and the treatment hypotheses; however, treatment dose becomes apparent over time. Due to the nature of the SMT and light massage treatments, providers and patients are not blinded to treatments at each visit. Qualitative interviewers and project managers at both sites are not blinded.

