##### Qualitative analysis

For the qualitative interviews, content analysis using an inductive approach [76] will be used to identify categories and themes that occur in the transcribed text [77]. Transcribed data will be entered into a database designed to capture and analyze qualitative data. The frequency of themes will be quantified and representative quotations will be identified [77, 78]. The frequency of responses in the thematic categories will be cross-tabulated with treatment group assignment and compared for between group differences using Chi-square analysis. 95% confidence intervals will be calculated for these differences.

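### Unblinded interviewers gather the themes that are then tested between randomized arms, so differences in theme frequency cannot safely be read as effects of SMT dose

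*Protocol article*

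**What the plan says.** - **Label.** The Abstract and the Study overview describe the trial as observer-blind, in the latter as "This study is a two-site, prospective, parallel groups, observer-blinded, randomized controlled trial".
- **Who is blinded.** The Blinding section specifies: "Research staff who perform clinical and objective examinations and data entry are blinded to treatment assignment".
- **Who is not.** The same section says that "providers and patients are not blinded to treatments at each visit", that dose is at first concealed from both but "however, treatment dose becomes apparent over time", and that "Qualitative interviewers and project managers at both sites are not blinded".
- **The interviews.** According to Data collection, "Qualitative interviews are also conducted at the end of treatment". The Qualitative interviews section makes them face to face and semi-structured, held at week 6 by trained staff who follow an interview schedule. They cover views of treatment, expectations and experience of headache. On technique it says: "Questions start broadly and are followed-up with probing questions to elicit additional information".
- **The analysis.** In the Qualitative analysis section, theme frequencies are "cross-tabulated with treatment group assignment and compared for between group differences using Chi-square analysis", with 95% confidence intervals for the differences. The preceding section calls the structural-equation path analysis exploratory. The theme comparison carries no such label.

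**The concern.** In a semi-structured interview the interviewer helps to produce the data. Which answers are followed up, and how far, affects whether a theme appears in the transcript at all. An interviewer who knows that a participant had 18 manipulation visits rather than none may, without intending it, pursue some topics harder in one arm than in another. That is tolerable when the material is only described. Here it enters a formal comparison between randomized arms.

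Randomization makes the arms comparable at entry, but it does not protect against measurement that differs by arm. A theme equally common in all four arms could be recorded at different rates, and the chi-square test cannot distinguish this from a real difference in patients' views. A small p-value or a confidence interval excluding zero would then be reported as an effect of SMT dose on expectations. The Discussion presents the combined qualitative and quantitative study of dose and expectations as, to the authors' knowledge, a first, so readers are likely to give these comparisons weight.

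**Working it through.** **Tracing the path through the document**

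1. Interviewers are not blinded (Blinding). This is stated outright.
2. They probe face to face on treatment views, within an interview schedule (Qualitative interviews). A schedule steers topics, but follow-up probes still leave room for judgement.
3. The themes are counted and tested by assigned group (Qualitative analysis).
4. Neither that section nor the Blinding section says whether the coders know the arm. The coding route is therefore conditional; the elicitation route rests on stated facts.

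**How large could the effect be?**

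The article gives no number of interviews, theme prevalence, significance level for theme tests or size of interviewer effect, so there is no stated figure to reproduce. Everything below is illustrative.

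Inputs:
- Four arms (0, 6, 12 and 18 SMT visits) with 64 randomized to each: Treatment dose section.
- *Assumed:* everyone is interviewed, so n = 64 per arm; true prevalence is 30% in every arm; α = 0.05; knowledge of the arm adds s to the recorded prevalence at each dose step.

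Recorded prevalences are p_k = 0.30 + s·k for k = 0, 1, 2, 3. The noncentrality of the Pearson test is λ = n·Σ(p_k − p̄)² / [p̄(1 − p̄)]. The rejection probability is P(χ²(df, λ) > critical value), with 3 df for four arms and 1 df for 0 versus 18 visits.

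*s = 0.03, four arms.* p̄ = 0.345 and Σ(p_k − p̄)² = 2(0.045² + 0.015²) = 0.0045. λ = 64 × 0.0045 / (0.345 × 0.655) = 0.288 / 0.2260 = 1.27. Rejection: **13.6%**.

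*s = 0.03, 0 versus 18.* λ = 64 × 2 × 0.045² / 0.2260 = 0.2592 / 0.2260 = 1.15. Rejection: **18.8%**.

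*s = 0.05, four arms.* p̄ = 0.375 and Σ = 2(0.075² + 0.025²) = 0.0125. λ = 64 × 0.0125 / (0.375 × 0.625) = 0.8 / 0.2344 = 3.41. Rejection: **30.9%**.

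*s = 0.05, 0 versus 18.* λ = 64 × 2 × 0.075² / 0.2344 = 0.72 / 0.2344 = 3.07. Rejection: **41.8%**.

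**Range over the assumptions**

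The four-arm test was also simulated (40,000 replicates per setting) with true prevalences of 20%, 30% and 50%:

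| Recording bias, highest versus 0-visit arm | Pattern | n = 64 per arm | n = 32 per arm |
|---|---|---|---|
| none | – | about 5% | about 5% |
| 5 points | graded with dose | 7–8% | 6% |
| 10 points | graded with dose | 15–18% | 10–11% |
| 10 points | same in all three SMT arms | 19–23% | 12–13% |
| 20 points | graded with dose | 52–58% | 27–30% |

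The table shows how sensitive the test is to a given bias. It does not show that any bias exists. With fewer interviews or a smaller bias, the inflation shrinks.

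**The case against.** The case on the other side is strong in several respects.

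**The label is disclosed, not contradicted.** A reader might infer that calling the trial observer-blinded is false, or that it lends the primary result a protection it lacks. The document does not support that. The Blinding section names both the blinded staff, including those doing data entry, and everyone who is not blinded. The Abstract calls the primary outcome patient-reported in the same paragraph as the label, and the Discussion acknowledges that expectation is managed without blinding. At most, the short label could be made more specific.

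**Probing is not unrestricted.** The interviewers are trained and follow a schedule. This reduces arm-dependent probing but does not exclude it. The schedule is not shown, so nothing can be said about whether it requires knowledge of the dose.

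**Coder masking may be set out elsewhere.** An article commonly leaves this to the full protocol or analysis plan, so its absence here is no finding. The point rests on the stated unblinding of interviewers; coding enters only conditionally.

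**The primary outcome is not reached.** A reader might infer that a week-6 conversation with unblinded staff contaminates the headache counts for the 4 weeks before weeks 12 and 24. That is speculation. The counts come from a self-completed daily diary, preferably by text message or email. Those windows open about 2 and 14 weeks after the interview, and participants already know from their own visits what they received.

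**The rates assume the bias they display.** This is correct. They measure sensitivity only.

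**Blinding interviewers would achieve little.** This is largely right, since participants talk about their treatment. Enrollment is also complete (Study status), so most interviews have probably been held.

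What remains is the combination of unblinded, probed elicitation with formal tests between arms that carry no exploratory label.

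**Conclusion.** The point holds, within limits. Interviewers who are not blinded elicit themes by probing, and those themes are then tested between randomized arms as if they had been measured alike in each. A nominally significant difference could reflect the interviewer's knowledge of the arm, or the coder's if coders have it, rather than the SMT dose.

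The size and direction of any such bias cannot be derived from the document. On the assumed values, a drift of 3 points per dose step would take a 5% four-arm test to about 14%, and one of 5 points per step to about 31%. Both figures depend on 64 interviews per arm and 30% prevalence.

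The consequence is limited to the qualitative part of the tertiary aim. The primary diary outcome and the sample size are unaffected. The change is still worth making, because it governs what may be concluded from the theme comparisons and can be made at the analysis stage.

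**What to change.** 1. **Qualitative analysis section.** Code transcripts with arm labels removed and explicit mentions of dose masked where possible. Lock the codes before linking them to allocation.
2. **Same section.** Report the theme-by-arm comparisons as exploratory, and state interviewer unblinding as a limitation. This is needed even with masked coding, because masking cannot undo differences that arose during the interview.
3. **Blinding section.** For any interviews still to be held, do not give interviewers the allocation.
4. **Optional, Abstract and Study overview.** State that observer-blinded refers to the clinical and objective examinations and to data entry, and that patient-reported outcomes come from participants who are not blinded to treatment.

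The cost is some redaction of transcripts and a few sentences of wording. No new patients are needed and the primary analysis does not change. Masking will be only partial, because participants describe their treatment in their own words. Steps 1, 2 and 4 do not depend on enrollment, which is complete.

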### Recruitment

Potential subjects are recruited from Minneapolis, MN, Portland, OR and their surrounding metropolitan communities using multiple recruitment methods. These include systematic mailings of study post-card mailers, online advertisements (Craigslist, Facebook, news websites), local radio, newspaper and community postings, and referrals from community medical clinics.

### Study population

Adults, age 18 and older with a history of chronic CGH are eligible to participate. The eligibility criteria are described in Table 1. Participant flow (Fig. 1) data are recorded in accordance with the Consolidated Standards of Reporting Trials (CONSORT) [31] statement and will be reported with final study results.

**Table 1 Tab1:** Inclusion and exclusion criteria

Inclusion criteria	Exclusion criteria
- 18 years of age and older - History of CGH ≥ 3 months at Baseline 1, ≥5 days of CGH per month - CGH intensity ≥3 (0–10 scale) - Cervical spine dysfunction (cervical joint tenderness and/or restricted segmental motion) - Clear temporal sequence linking the source of CGH to the neck: headache preceded by neck pain, stiffness, movement and/or awkward postures - English literate - Independent ambulation	- Other headaches within one year of enrollment (e.g. migraine occurring on >1 day per month in the last year, medication overuse, daily, cluster, temporomandibular joint dysfunction related headaches, sinus, posttraumatic, tumor and glaucoma related, occipital neuralgia, metabolic/toxic/substance abuse related). - Spinal manipulative therapy, massage or exercise therapy for neck pain or headaches in the previous 3 months. Any other types of care by a licensed provider in the previous month for headaches or neck pain - Contraindications to study treatments (e.g., inflammatory arthropathies, cervical instability, severe osteoporosis, vertigo, dizziness) - Daily prescription or nonprescription pain medication; corticosteroid use in previous month - Cancer in the past five years - Cardiovascular comorbidities (e.g., history of stroke, transient ischemic attacks, stage 2 hypertension, taking anticoagulant medication, syncope, myocardial infarction, hemophilia) - Neurological comorbidities (e.g., multiple sclerosis, ALS, Parkinson’s, myelopathy, seizures, cervical radiculopathy, herniated disc, thoracic outlet syndrome, brachial plexus neuropathy) - Spinal pathology (e.g., infection, tumor, fracture, diffuse idiopathic skeletal hyperostosis, degenerative joint disease, stenosis) - Involved in a research study about pain - Active or pending medical litigation, personal injury, workers compensation; disability compensation - Noncompliance with headache diary at baseline (<24/28 days completed); pre-randomization noncompliance - Pregnancy, trying to get pregnant, 3 months post-partum - Brain or cervical spine surgery in previous 5 years; trauma to head or neck requiring hospitalization in previous year - Severe, unmanaged depression

**Fig. 1 Fig1:**
[figure not shown]
Participant flow

### Changes to the study protocol

Initially, participants with a history of migraine headaches in the last year were excluded. In the second year of the study, this criterion was modified to exclude participants who had >1 migraine headache day per month in the last year. The primary rationale for this change was to enhance recruitment and enrollment at both sites. The likelihood that this change is a major confounder is low due to the infrequent nature of included migraine headaches, the distinct nature of the symptoms [5], and study participants ability to recognize migraine and cervicogenic headaches as different. In addition, the analysis was modified to include stratification by the presence or absence of migraine headaches.

### Definition and diagnosis of cervicogenic headache

CGH is identified as a distinct classification of headache by the International Classification of Headache Disorders [5]. The diagnostic criteria used are shown in Table 2 [32]. Criterion D is not used to diagnose cervicogenic headache or determine enrollment in this study; this criterion is not relevant in prospective treatment studies.

**Table 2 Tab2:** Cervicogenic headache diagnostic criteria (ICHD 2^nd^ Edition)

A.	Pain, referred from a source in the neck and perceived in one or more regions of the head and/or face, fulfilling criteria C and D.
B.	Clinical, laboratory and/or imaging evidence of a disorder or lesion within the cervical spine or soft tissues of the neck known to be, or generally accepted as, a valid cause of headache.
C.	Evidence that the pain can be attributed to the neck disorder or lesion based on at least one of the following:
	1. Demonstration of clinical signs that implicate a source of pain in the neck.
	2. Abolition of headache following diagnostic blockade of a cervical structure or its nerve supply using placebo- or other adequate control.
D.	Pain resolves within 3 months after successful treatment of the causative disorder or lesion.

Key: *ICHD* international classification of headache disorders

Participants undergo a thorough headache history at baseline to confirm a temporal sequence exists linking the headache to the neck. A manual exam of the cervical spine is conducted to identify areas of joint dysfunction [33]. Participants who meet these criteria, without symptoms suggestive of a different headache (e.g., prodromal aura, sensitivity to light and sound), are diagnosed with CGH.

### Eligibility determination

#### Phone screen

Potential participants respond to recruitment materials and trained interviewers conduct telephone screens to assess obvious eligibility criteria. Suitable candidates are then scheduled for the first of two baseline evaluation appointments within 60 days of the phone screen.

#### Baseline 1 evaluation

The first baseline evaluation (BL1) includes an in-person informed consent. Participants complete a self-report questionnaire, and undergo a health history, physical examination, and cervical radiographs, which are used to rule out contraindications to treatment (e.g., diffuse idiopathic skeletal hyperostosis, severe degenerative joint disease). Previous medical records are also obtained as needed to rule out contraindications. A trained and certified examiner performs a blinded, objective assessment of cervical spine motion, and static and dynamic pain pressure thresholds. Qualified participants at BL1 are scheduled 4 weeks later for the baseline 2 screening evaluation (BL2). In the interim, participants complete a daily headache diary to capture CGH frequency and intensity, medication use, and other types of headaches.

#### Case review meetings

Following BL1, study personnel review each case weekly to determine preliminary study eligibility. Patient safety and compliance concerns are also addressed. These meetings ensure consistent interpretation and application of the pre-defined eligibility criteria. Consensus is reached for all cases and recommendations for inclusion, exclusion, or follow-up care are made.

